## Abstract

**Background:**

Insomnia is a significant risk factor for depression onset, can result in more disabling depressive illness, and is a common residual symptom following treatment cessation that can increase the risk of relapse. Internet-based cognitive behavioural therapy for insomnia has demonstrated efficacy and acceptability to men who are less likely than women to seek help in standard care. We aim to evaluate whether internet delivered cognitive behavioural therapy for insomnia as an adjunct to a standard depression therapeutic plan can lead to improved mood outcomes.

**Methods/Design:**

Male participants aged 50 years or more, meeting Diagnostic and Statistical Manual of Mental Disorders criteria for current Major Depressive Episode and/or Dysthymia and self-reported insomnia symptoms, will be screened to participate in a single-centre double-blind randomised controlled trial with two parallel groups involving adjunctive internet-delivered cognitive behavioural therapy for insomnia and an internet-based control program. The trial will consist of a nine-week insomnia intervention period with a six-month follow-up period. During the insomnia intervention period participants will have their depression management coordinated by a psychiatrist using standard guideline-based depression treatments. The study will be conducted in urban New South Wales, Australia, where 80 participants from primary and secondary care and direct from the local community will be recruited. The primary outcome is change in the severity of depressive symptoms from baseline to week 12.

**Discussion:**

This study will provide evidence on whether a widely accessible, evidence-based, internet-delivered cognitive behavioural therapy for insomnia intervention can lead to greater improvements than standard treatment for depression alone, in a group who traditionally do not readily access psychotherapy. The study is designed to establish effect size, feasibility and processes associated with implementing e-health solutions alongside standard clinical care, to warrant undertaking a larger more definitive clinical trial.

**Trial registration:**

Australian and New Zealand Clinical Trials Registry ACTRN12612000985886.

## Background

Symptoms of insomnia are commonly comorbid with depression, particularly in older adults [1]. In this population, although advanced sleep phase can occur, insomnia is the most commonly reported sleep disturbance; this includes complaints of difficulty falling asleep, frequent nocturnal awakenings, and early morning wakefulness [2,3]. These lead to shorter overall sleep duration, which in turn contributes to chronic patterns of mental ill health [4]. Epidemiological studies suggest that insomnia is a significant risk factor for depression onset and recurrence in both younger and older samples [5-7]. Insomnia comorbid with depression is indicative of a more severe illness and, despite its implications, tends to be under-treated [5]. In late life depression, sleep disturbance appears to be most prominent at the onset of the episode [8] and has been shown to be a prognostic marker [9,10]. Insomnia may be separate or reflect an inadequately treated episode of Major Depressive Disorder (MDD). Reports of the prevalence of residual insomnia symptoms in those responding to treatment for MDD, range from 30% up to 90% [11]. Importantly, failure to achieve full remission from even the first episode of MDD is a strong predictor of recurrence and chronicity as shown in landmark National Institute of Mental Health studies [12] and confirmed in the STAR-D trial [13]. Further, insomnia is the most common residual symptom after completion of drug or therapeutic treatment of mood disorder [11,12] occurring in up to two thirds of this group in the STAR-D study [13]. Thus insomnia in elderly people with previous MDD is a strong and independent predictor of recurrent [10] and persisting MDD [9].

The question of whether adjunctive treatment of insomnia can improve the standard treatment of depression was addressed in a pilot trial by Manber et al. [14]. They reported that the addition of seven sessions of cognitive behavioural therapy for insomnia (CBTi) to escitalopram resulted in a higher rate of remission of depression (61.5%) than in the control arm (33.3%). The adjunctive therapy was also associated with a greater remission from insomnia (50.0%) as compared to control (7.7%) and larger improvement in all diary and actigraphy measures of sleep, except for total sleep time. More recently, Watanabe et al. [15] demonstrated that four weekly face-to-face sessions of CBTi as a supplement to outpatient treatment in psychiatric clinics was associated with higher rates of remission of depression (50.0%) compared with treatment as usual (6.0%), with similarly favourable rates of remission for insomnia (50.0% versus 0.0%). This study has since been extended by Wagley et al. [16] using a briefer version of face-to-face CBTi in a broader sample of patients with psychiatric disorders, which has also shown significant reductions in both depressive symptoms and sleep quality following treatment.

Men with symptoms of depression and anxiety, particularly in the oldest and youngest age groups seek help far less frequently than women for a given threshold or condition [17]. Whilst help-seeking for depression remains low, over half of people with insomnia seek treatment in primary care [18] making it likely that an insomnia intervention program would be well received and utilised. Internet-based programs have some distinct advantages in the delivery of treatment and prevention services. Treatment using e-health applications is 20 times more cost effective than face-to-face psychological treatment and 50 times more efficient than medication in terms of disability-adjusted life years averted [19]. However, we are not aware of any study evaluating the use of adjunctive internet-based CBTi in older men with depression.

With the development and initial evaluation of Sleep Healthy Using the Internet (SHUTi), members of our team have demonstrated the efficacy of an internet intervention for adults with insomnia [20]. This intervention is firmly grounded in the research supporting the efficacy of face-to-face CBTi [21], including the primary components of sleep restriction, stimulus control, cognitive restructuring, sleep hygiene, and relapse prevention. SHUTi is an interactive, self-help program, which is fully automated and based on principles of self-help. In this community-based study of adults with insomnia [20], participants randomly assigned to receive SHUTi not only experienced significant sleep improvements, but also demonstrated improvements in comorbid psychological symptoms and quality of life, compared to those in a wait-list control group [22].

As such, we hypothesise that providing SHUTi as an adjunct to standard care in older men with comorbid depression and insomnia symptoms will improve depression more than an adjunctive controlled website providing insomnia education alone.

### Objectives

In older men with major depression, this trial aims to:Investigate the efficacy of SHUTi as an adjunctive treatment to standard *beyondblue* guideline-based treatment [23,24] for reducing depression symptom severity;Determine whether adjunctive SHUTi decreases anxiety and insomnia symptom severity;Ascertain whether SHUTi is associated with changes in actigraphy/sleep diary determined sleep in people with comorbid depression and insomnia symptoms;Explore the processes, predictors and mediators of treatment response and of adherence to SHUTi by determining user characteristics and behaviours that may predict positive outcomes, adherence, trial drop-out, and program acceptability.

## Methods/Design

### Trial design

The study is a single-centre double-blind randomised controlled trial (RCT) with two parallel groups involving an internet-delivered CBTi intervention and an insomnia education control condition. The trial consists of a nine-week insomnia intervention period and six-month follow-up period. The intervention will be delivered as an adjunct to standard guideline-based treatment for depression. As such, during the intervention period, participants in both arms will have their depression assessed, and the treatment managed, by a psychiatrist in accordance with clinical practice guidelines [23,24]. At trial entry, and after randomisation, participants will complete baseline clinical, sleep and self-report measures over two-weeks. They will then commence their internet-delivered CBTi program / web-based insomnia education (control) and continue with it over the subsequent nine-weeks. Participants will be contacted by telephone at Week 4 and Week 8 for trial monitoring purposes. At Week 12, they will commence the post-intervention assessment and will repeat the clinical, sleep and self-report measures collected at baseline. Throughout this period they will have face-to-face sessions with the psychiatrist, their General Practitioner (GP) and other health professionals, as clinically required, to manage their depression. Six months after completion of the post-intervention assessment, participants will complete the self-report, psychological and sleep measures. As such there will be three principal occasions of measurement over the full study period: baseline, post-intervention, and 6-months post-intervention, and the primary endpoint will be a reduction in depressive symptoms at post-intervention (week 12). The total trial period will be nine months. The trial has been registered on the Australian and New Zealand Clinical Trial Registry (ACTRN12612000985886). The trial design is shown graphically in Figure 1.

**Figure 1 Fig1:**
[figure not shown]
**Proposed flow of participants.**

### Study setting

The target population for the SOMNA trial is Australian male adults, aged 50 years and over, who meet diagnostic criteria for a current depressive disorder and self-reported sleep disturbance. Participants will be recruited from local primary and secondary care providers, as well as directly from the local community via newspaper and radio advertisements, community organisation newsletters and events. An online recruitment and marketing campaign will also be implemented through help-seeking websites and social media.

### Eligibility criteria

Participants eligible for the SOMNA trial must comply with all of the following at the point of randomisation:Have a depressive disorder, defined as screening positive (score greater than or equal to 8) on the Quick Inventory of Depression Symptomology Self Report (QIDS-SR) [25] at preliminary screening, and meeting Diagnostic and Statistical Manual of Mental Disorders (DSM-IV) criteria for current Major Depressive Episode and/or Dysthymia at clinical interview using the Structured Clinical Interview for DSM-IV (SCID) [26];Report insomnia symptoms above threshold (score greater than or equal to 8) on the Insomnia Severity Index (ISI) [27] at preliminary screening; and,Have provided written informed consent before any trial procedures are undertaken.

Participants will be excluded from participating in the SOMNA trial if at the point of randomisation they:Have a prior history of psychosis or hypo/manic episodes, determined either during phone screening or at clinical interview;Have current substance dependence, determined at clinical interview;Score less than 24 on the Mini Mental State Examination (MMSE) [28], determined at clinical interview;Are a rotating shift worker with overnight shifts;Have undertaken transmeridian travel in the past month, where the time difference is greater than two hours and there has been an inadequate period to readjust to local time (adjustment defined as requiring 48 hours for every one hour time difference);Meet criteria for Restless Legs Syndrome (RLS) as defined using the Cambridge-Hopkins RLS short form diagnostic questionnaire [29];Are at high risk for obstructive sleep apnea (OSA) as defined by the Berlin Questionnaire [30], or have been treated for sleep apnea.

### Interventions

All eligible participants will be randomised on a 1:1 basis to receive either SHUTi or the web-based insomnia education control program.

#### Active treatment arm: SHUTi

The Sleep Healthy Using the Internet (SHUTi, http://shuti.me) program is firmly grounded in research supporting the efficacy of face-to-face Cognitive Behavioural Therapy (CBT) for insomnia [20]. Described in detail elsewhere [31], SHUTi consists of six core modules addressing behavioural, educational and cognitive techniques, incorporating sleep restriction and stimulus control, sleep hygiene, cognitive restructuring and relapse prevention. Content is presented in an interactive format featuring text, graphics, audio and animations. The program utilises vignettes and quizzes to deliver information, and provides individually tailored recommendations to help improve sleep as informed from sleep diary information submitted by users. The six core modules are available to complete sequentially and completion involves up to an hour per week, over a nine-week period. Participants are also encouraged to submit daily sleep diaries each week. An automated email notifies participants that a new module is available for completion. At the beginning of each new module, participants receive recommendations for sleep restriction treatment based on their completion of the previous weeks online daily sleep diaries, along with a review of relevant information from previously completed modules. Participants are able to move forward to the next module one week after the previous module is completed in full. Automated midweek reminders to enter sleep diaries, implement strategies and commence the next module are also sent. Each module remains available once it has been completed so participants may review all program content.

#### Control arm

The insomnia education control program provides credible sleep health information addressing the impact and prevalence of insomnia, along with common causes and symptoms of insomnia. It provides limited sleep hygiene information pertaining to lifestyle and environmental factors that may affect sleep. While behavioural and cognitive techniques are mentioned in the control program, unlike SHUTi, the strategies are not obtainable in a tailored, metered, or interactive fashion, but rather the content is presented in a basic text format only. Consideration of the content requires approximately 30 minutes. However, the insomnia education program (but not sleep diaries) is available for further review by participants at any time over the nine-week intervention period.

### Clinical treatment for depression

As part of standard treatment for depression, all participants will undergo a clinical assessment with a psychiatrist prior to study commencement, whereupon a depression treatment plan will be prepared in accordance with clinical practice guidelines [23,24]. This will include watchful waiting, referral to psychotherapy or other interventions such as couple therapy, or medication use under standard collaborative care with the patient’s GP. The assessment will include the Mood Episode and Disorder modules, and the Substance Abuse screens of the SCID, standard clinician rated measures: the 17-item Hamilton Rating Scale for Depression (HAM-D) [32], and the Hamilton Rating Scale for Anxiety (HAM-A) [33], Mini Mental State Examination [28], Global Assessment of Functioning (GAF) [34], Social and Occupational Functioning Assessment Scale (SOFAS) [35] and Cumulative Illness Rating Scale for Geriatrics (CIRS-G) [36] as well as completion of a full psychiatric and medical history. After two weeks, participants will be required to undergo a clinical review with the psychiatrist, in accordance with their treatment plan. Over the subsequent nine weeks, participants will undergo further psychiatric review and management as clinically required. Standard clinical instruments will be administered to monitor depressive symptoms over this period. If any changes to medication dosage are required, this will be discussed between the patient, trial psychiatrist and/or referring doctor. At the end of the trial period the participant will be referred back to their GP or treating doctor, or if required, managed in the trial clinic until appropriate for discharge.

### Participant monitoring and program adherence

While individual completion of SHUTi and the insomnia education control programs will be systematically tracked using methods embedded in the website infrastructure, their completion (or otherwise) will be achieved without any direct supervision or encouragement from the trial team. Participants will be able to seek technical support as needed (e.g. if a username or password is forgotten) but as this is a trial of an adjunctive insomnia treatment, no specific clinical support will be provided. Furthermore, as all participants will be under the clinical care of their treating psychiatrist, safety and general monitoring will be conducted at each scheduled clinical review and follow-up appointment(s). Research assistants will contact all participants by telephone at Week 4 and Week 8 (as indicated in Figure 1) whereby data will be collected against the primary and secondary outcome measures, addressing mood state and insomnia symptoms. Participants demonstrating deterioration in mood state will be referred to their treating psychiatrist for risk management and follow-up.

### Self report measures

#### Primary outcome

The primary outcome is change in severity of self-reported depressive symptoms from baseline to three months, as measured by the Centre for Epidemiological Studies Depression scale (CES-D) [37]. The 20 items in the CES-D measure symptoms of depression over the past week on a 0–3 scale, and provide a summary score ranging from 0 to 60 with higher scores indicating the presence of greater depressive severity. Although originally created for the general population, the CES-D is a reliable and valid measure of depressive symptoms and widely used in clinical populations [38]. A self-report measure, the CES-D will be embedded into each of the formal assessments at baseline, post-intervention and six-month post-intervention follow-up. The change in severity of clinician-rated depressive symptoms over a three-month period, will also be determined using the HAM-D [32]. Considered the gold standard depression assessment tool, the HAM-D is the most widely used clinician-administered scale in clinical trials of antidepressant treatment. It rates the severity of symptoms observed in depression such as low mood, insomnia, agitation, anxiety and weight loss, with higher scores indicative of more pronounced symptomatology. Mean changes in continuous depressive symptom scores from baseline will be compared between the two randomised groups at three-months. Change scores will be based on summed scores derived from the CES-D and the HAM-D respectively.

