### Sample size

In older adults, literature suggests depression treatment comprising pharmacotherapy or psychotherapy will elicit medium effects on symptomology. In the secondary analysis of the primary SHUTi trial, the effect of the intervention on depressive symptoms was larger than this, with a reported effect size on reducing depressive symptoms of 0.72 pre and post assessment using the Beck Depression Inventory [22]. Although noting this was detected amongst a community sample with mild depressive symptoms, we hypothesise that an adjunctive SHUTi intervention will lead to a small to moderate effect size over and above the effect of standard guideline-based depression treatment in a naturalistic setting. We propose to conduct a randomised controlled trial that will seek to establish the true effect size, along with feasibility of conducting a definitive clinical trial in a large-scale primary care setting that would provide evidence on the potential benefit of an adjunctive insomnia intervention for depression amongst older men. We will attempt to recruit a minimum of 80 participants with 40 per group (36 per group with 10% attrition) for the comparison of endpoint depression scores between the SHUTi intervention and the control condition.

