### Sequence generation

The allocation sequence will be generated using a randomly generated number sequence calculated used Research Randomizer (http://www.randomizer.org/) prior to trial commencement. The fully replicable sequence will be based on permuted blocks, and eligible participants will be stratified according to presenting depression severity (their summed HAM-D score obtained during the baseline medical assessment and clinical review) to ensure participants with higher levels of symptoms are distributed equally across both conditions. In accordance with severity classification that maximises the sensitivity and specificity of the HAM-D scale, symptom severity will be collapsed into two categories including *mild-moderate* scores <17; *moderate-severe* scores ≥17 [42]. The allocation sequences within each strata will be pre-generated by the unblinded trial manager and documented in the randomisation schedule prior to trial commencement.

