### Statistical methods

Primary outcome analysis will be undertaken on an intention-to-treat basis. Mixed-model repeated measures analyses will be used because of the ability of this approach to include participants with missing data. Characteristics of the participants including sociodemographics, physical activity, health and lifestyle factors will also be described by treatment group and overall. Safety criteria including adverse events and withdrawals will also be analysed. The type one error will be set at 5%. Descriptive statistics will include number of participants (N), mean, standard deviation, minimum, maximum and if a non- normal distribution, the median and first/third quartiles will be reported.

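### The primary CES-D comparison is worded as mean change, as endpoint score and as a mixed model; name one baseline-adjusted Week 12 contrast, because the change-score wording read literally is less precise

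*Protocol article*

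**What the plan says.** Three sections of the protocol article bear on how the arms are compared on the primary outcome.

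- **Primary outcome.** "The primary outcome is change in severity of self-reported depressive symptoms from baseline to three months", measured by the CES-D. The comparison is then spelled out: "Mean changes in continuous depressive symptom scores from baseline will be compared between the two randomised groups at three-months".
- **Sample size.** The 40 per group (36 after 10% attrition) are "for the comparison of endpoint depression scores between the SHUTi intervention and the control condition".
- **Statistical methods.** The primary analysis is by intention to treat, and "Mixed-model repeated measures analyses will be used because of the ability of this approach to include participants with missing data". No contrast, covariate or visit set is given.

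Two further items are collected and could serve the analysis.

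- **Sequence generation.** "eligible participants will be stratified according to presenting depression severity", with HAM-D split at below 17 versus 17 or more.
- **Weeks 4 and 8.** Under Participant monitoring and program adherence, at the telephone calls "data will be collected against the primary and secondary outcome measures, addressing mood state and insomnia symptoms", and Table 1 marks the CES-D there. The Trial design section says "there will be three principal occasions of measurement over the full study period" (baseline, post-intervention and six months later) and describes the calls as monitoring.

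**The concern.** Change from baseline and endpoint score are different variables with different variances, and tests on them can disagree in the same data. Naming a mixed model does not settle which is meant, because such a model can deliver either a change contrast or a baseline-adjusted contrast. The article therefore leaves the primary estimate and test open to choice.

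The only comparison spelled out for the primary outcome is the change score. Taken literally, it is less precise than adjusting for baseline CES-D, which every participant supplies. With about 72 evaluable men and an effect the Sample size section expects to be small to moderate, that precision is worth having.

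**Working it through.** **Inputs from the article.** 40 per group randomised, 10% attrition, 1:1 allocation, 5% type I error. The plan's own figure reproduces: 40 × 0.9 = 36 per group. Nothing further can be reproduced, since no power, SD or numerical effect is given.

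**Assumptions.** Two-sided test; equal CES-D SD (σ) at baseline and Week 12; baseline to Week 12 correlation r of 0.3, 0.5 or 0.7; true difference 0.5σ, taken as the upper end of small to moderate.

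**Step 1: variance of the arm difference, complete data.** In units of 2σ²/n:

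- endpoint score: 1
- change score: 2(1 − r)
- baseline-adjusted: 1 − r²

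Adjusted over change = (1 − r²) / [2(1 − r)] = (1 + r)/2.

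| r | endpoint | change | adjusted | cut vs change | cut vs endpoint |
|---|---|---|---|---|---|
| 0.3 | 1 | 1.40 | 0.91 | 35% | 9% |
| 0.5 | 1 | 1.00 | 0.75 | 25% | 25% |
| 0.7 | 1 | 0.60 | 0.51 | 15% | 49% |

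Change is worse than endpoint below r = 0.5, equal at 0.5 and better above it. Adjustment beats both for every r strictly between 0 and 1.

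**Step 2: power.** Two-sample t-test, 36 per arm, standardised difference 0.5/√(variance factor):

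| r | endpoint | change | adjusted |
|---|---|---|---|
| 0.3 | 55% | 42% | 59% |
| 0.5 | 55% | 55% | 68% |
| 0.7 | 55% | 77% | 83% |

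The adjusted column ignores the one degree of freedom spent on the covariate. At a difference of 0.2σ, power is only 11% to 22% across all the cells, so no choice of analysis rescues a small effect.

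**Step 3: does the mixed model settle it?** Take 40 per arm, with 4 per arm missing Week 12, r = 0.5, σ = 1, and baseline and Week 12 only. The generalised least squares variance of the arm contrast is:

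- each arm's baseline mean free, contrast = Week 12 minus baseline: 0.0542
- one common baseline mean (equivalent in precision to adjustment): 0.0417

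1 − 0.0417/0.0542 = 23% lower. Both are mixed-model repeated measures analyses; the first matches the literal change wording.

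**Step 4: Weeks 4 and 8.** Adding these visits to the same model, with r from 0.4 to 0.7 and the missing men lost after Week 8:

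- Smallest gain (compound symmetry, r = 0.4, free baselines): 0.0647 to 0.0641, about 1%.
- Largest gain (first-order autoregressive, r = 0.7, common baseline): 0.0283 to 0.0267, about 6%.
- With complete Week 12 data and a common baseline mean the variance is unchanged (0.0375 with or without them at r = 0.5).

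**Step 5: HAM-D stratum.** Its gain needs the correlation of the stratum with Week 12 CES-D, which the article does not give. Leaving out a stratification factor does not bias the estimate; it tends to make the standard error conservative.

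**The case against.** The strongest defence is that these sections have different jobs: one defines the outcome, one motivates the sample size and one gives the method. A mixed model can estimate the arm difference in change at Week 12, so Primary outcome and Statistical methods can be read together. Once baseline is a covariate, the adjusted difference in change and in Week 12 score are the same number. This stands in part. The plainest mismatch is endpoint scores in Sample size against change in Primary outcome, and no section says which contrast is primary.

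A reader might infer that no planned analysis uses baseline CES-D, the stratum or the Week 4 and 8 scores, and that precision is therefore lost. The article does not support that. Statistical methods is silent on covariates and visits, which excludes nothing, and such detail is commonly left to an analysis plan. A mixed model with a common baseline mean already has adjusted precision.

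A reader might also infer that omitting Weeks 4 and 8 defeats the stated reason for the mixed model. The three occasions are called principal or formal; they do not define the model's visits, and Step 4 shows that the amount at stake is small.

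Finally, the trial aims to establish an effect size and feasibility for a larger study, not to meet a power target. That softens the power figures, but a precise estimate matters as much for that aim.

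**Conclusion.** The concern holds in a limited form. The primary comparison is worded inconsistently across three sections, and the one comparison spelled out is, if followed literally, less efficient than a baseline-adjusted one. Adjustment would remove 35% to 15% of the change-score variance for r from 0.3 to 0.7. The loss is conditional: it arises if the change wording is implemented as written, and not if the mixed model adjusts for baseline or uses a common baseline mean. Weeks 4 and 8 are a minor supporting point. The benefit of the stratum cannot be sized from the article. The figures rest on assumed values for r, the effect, equal SDs and a two-sided test. This should be changed because the remedy is better and nearly free; it is not a flaw that invalidates the trial.

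**What to change.** State one primary analysis, in the same words, in Primary outcome, Sample size and Statistical methods: the Week 12 arm difference in CES-D from the mixed model, adjusted for baseline CES-D and the HAM-D randomisation stratum (below 17, 17 or more). Say that Week 4 and Week 8 CES-D enter as post-baseline visits. Covariance structure, baseline-by-visit terms and whether the six-month score enters can be left to the analysis plan.

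The cost is wording only, since every variable is already scheduled. One caution: Weeks 4 and 8 are collected by telephone, and later assessments may also be by post or telephone for some men. Mode is thus not fixed by visit, and a visit term need not absorb all of its effect.
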